##### Secondary endpoints

The willingness to repeat the procedure is defined as readiness of the patient to repeat the examination under the same conditions and will be recorded in the CRF with tick boxes (yes/no) by a nurse or physician. Heart rate (beats per minute), blood pressure (mmHg) and oxygen saturation (per cent) will be assessed before EGDE, after passage of the larynx and after removal of the endoscope. The results will be documented in the CRF by a nurse or physician. The duration of the examination in minutes from insertion to removal of the endoscope will be documented in the CRF. Furtheremore periinterventional complications as described and defined in Table 2 will be documented.

**Table 2 T2:** Definitions of periinterventional complications:

Complication	Definition
Haematoma	Clinical diagnosis

Bleeding	Clinical diagnosis

Nerve irritation	Clinical diagnosis

Bradycardy	Heart rate < 60 beats per minute

Hypotension	Blood pressure < 90 mmHg systolic

Low oxygen saturation	Oxygen saturation < 92%

Aspiration	Clinical diagnosis and radiological findings

Wound infection	Clinical diagnosis

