#### Study treatment

Patients who are scheduled for EGDE will be screened and informed by a member of the IEZ about the trial before their EGDE procedure. After signing the informed consent form the patients will be prepared by staff nurses for the procedure as usual. A study nurse or physician will be present to monitor and document the procedures (Table 1).

**Table 1 T1:** Study Visit Schedule

	Day of screening and intervention
Past medical history*	X

Informed consent	X

Personal data**	X

Examination of primary endpoints:	X
• Success of EGDE	

Examination of secondary endpoints:	
• Heart rate	X
• Blood pressure	X
• Oxygen saturation	X
• Duration of examination	X
• Willingness to repeat examination under same conditions	X
• Periinterventional complications	X

Safety criteria AE, SAE (2.6)	X

*study-relevant past medical history, past surgical history

** height (cm), weight (kg), gender, smoking customs, chemotherapy, existence of false teeth

All patients will be positioned on a stretcher lying on their backs with 30 degrees reverse Trendelenburg's position. Standard monitoring with SaO_2 _and non-invasive blood pressure will be established. Pharyngeal anaesthesia will be performed with a topical xylocaine spray (AstraZeneca, Germany) in all patients by a nurse or physician.

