**Figure 3 F3:**
[figure not shown]
Inserted acupuncture needle

KG 24   Chengjiang   middle line (to reduce choking)[15]

Pericard 6   Neiguan   bilateral   (to reduce gastroenteral motility)[16]

Di 4   Yangxci   bilateral   (to reduce nausea and vomiting)[17]

Half to one inch 32G needles (0.32 × 30 mm stainless steel needle from asia med company, Munich, Germany) will be placed and left in their position for five minutes prior and throughout the endoscopic procedure.

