##### Intervention-group B (real acupuncture)

After the described preparation patients will receive a real acupuncture at the following acupuncture points:

KG 24   Chengjiang   middle line   (to reduce choking)[15]

Pericard 6   Neiguan      bilateral      (to reduce gastroenteral motility) [16]

Di 4   Yangxci      bilateral      (to reduce nausea and vomiting)[17]

Half to one inch 32G needles (0.32 × 30 mm stainless steel needle from asia med company, Munich, Germany) will be placed into these points, stimulated for 1-2 seconds to induce de qi sensation and left in this position for five minutes prior and throughout the endoscopic procedure.

To perform EGDE all patients in both groups will be turned on their left side still with a 30 degree reverse Trendelenburg's position.

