##### Further analysis

In addition to the evaluation of the FAS, a PP analysis will be performed including all randomized patients without major protocol violations.

The secondary variables will be analyzed in a descriptive manner by tabulation of the measures of the empirical distributions. According to the scale level of the variables, means, standard deviations, medians, 1^st ^and 3^rd ^quartiles as well as minimum and maximum or absolute and relative frequencies, respectively, will be reported. Descriptive p-values of the corresponding statistical tests comparing the treatment groups and associated 95% confidence intervals will be given.

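### Table 2 counts heart rate, blood pressure and saturation complications by fixed cut-offs with no reference to the patient's own starting value, and the first reading is not fixed before needling

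*Protocol article*

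**What the plan says.** The Secondary endpoints section of the protocol article schedules heart rate, blood pressure and oxygen saturation at three moments: they "will be assessed before EGDE, after passage of the larynx and after removal of the endoscope". The same section refers to Table 2 for the definitions of periinterventional complications. Bradycardia is "Heart rate < 60 beats per minute"; hypotension and low saturation likewise have one fixed limit each (systolic pressure below 90 mmHg, saturation below 92%). None of the three carries a new-onset condition, a change from the starting value or a time window.

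On needle timing, the section on group B (real acupuncture) has the needles "stimulated for 1-2 seconds to induce de qi sensation and left in this position for five minutes prior and throughout the endoscopic procedure". The section on group A (placebo) says they "will be placed and left in their position for five minutes prior and throughout the endoscopic procedure", and describes no stimulation step.

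The Study treatment section places the start of monitoring ahead of the allocation-specific steps: "Standard monitoring with SaO_2 _and non-invasive blood pressure will be established". It does not say that a reading is recorded then.

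Eligibility excludes ASA V patients but sets no limit on resting heart rate, blood pressure or saturation.

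For secondary variables, Further analysis promises summary tables and "Descriptive p-values of the corresponding statistical tests comparing the treatment groups and associated 95% confidence intervals will be given". It names no test or model.

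**The concern.** A complication definition should separate what happened during the procedure from what the patient brought to it. Table 2 does not. A patient with a heart rate of 56 before needling who remains at 56 throughout meets the bradycardia definition although nothing has changed. This is true even if only the readings after passage of the larynx and after removal are classified. Eligibility does not screen such patients out.

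The natural reference would be the first reading, but its place relative to treatment is open. The interval just before endoscopy is a treatment interval in both arms, and only the real arm is described as stimulated. A reading taken then may already carry an effect of needling. If it served as the reference, a fall caused by the needles would look pre-existing. If it served as a baseline value in the homogeneity check, that check would compare treated patients. No later analysis can recover a pre-needling value that was not recorded.

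At stake is the safety statement. The article motivates the trial by the cardiopulmonary risk of sedation, so readers will look at these rates.

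**Working it through.** **The plan's own figure.** The article gives no number for vital signs or complications. Its only related figure is the primary sample size, checked here to show that it is separate. With 46% vs 61%, two-sided α = 0.05 and 80% power:

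n = [1.96·√(2·0.535·0.465) + 0.8416·√(0.46·0.54 + 0.61·0.39)]² / 0.15² = (1.3825 + 0.5869)² / 0.0225 ≈ 172.4, so 173 per group.

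Then 346 / 0.98 = 353.1, so 354. Both figures reproduce, and neither depends on Table 2.

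**Step 1: how many patients start below 60?** The mean and SD are assumptions. With a normal distribution and SD 12, P(rate < 60) = Φ((60 − mean)/12).

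| Assumed mean | P(rate < 60) | Of 354 |
|---|---|---|
| 70 | 20.2% | about 72 |
| 75 | 10.6% | about 37 |
| 80 | 4.8% | about 17 |

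Widening to means of 70-85 and SDs of 10-14 gives about 1% to 24%.

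**Step 2: what share of recorded bradycardia is pre-existing?** Let b be the proportion already low and p the true new-onset rate among the rest. If everyone already low is counted, the recorded rate is b + (1 − b)p and the pre-existing share is b / [b + (1 − b)p]. With b = 0.10 and p = 0.05 (both assumed):

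- recorded rate = 0.10 + 0.90 × 0.05 = 14.5%
- pre-existing share = 0.10 / 0.145 = 69%

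With b = 5% the share is 51%; with b = 20% it is 83%. If only procedural readings are classified and half of the 10% rise above the cut-off, the share is 0.05 / (0.05 + 0.045) = 53%.

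**Step 3: what happens to the comparison?** Assume true new-onset rates of 5% and 10%, the same b in both arms (as randomization gives in expectation) and 173 patients per arm. Power is for a two-sided chi-square test. The new-onset analysis uses the 173(1 − b) patients per arm who are not already low.

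| Already low | Recorded rates | Rate ratio (true 2.0) | Power, all counted | Power, new onset only |
|---|---|---|---|---|
| 5% | 9.8% vs 14.5% | 1.49 | 27% | 41% |
| 10% | 14.5% vs 19.0% | 1.31 | 20% | 39% |
| 20% | 24.0% vs 28.0% | 1.17 | 13% | 35% |

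The ratio moves towards 1 and both absolute rates rise. Neither arm is favoured. Power is low in either case, so the main gain from a new-onset count is a correct rate and ratio, not a decisive test.

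**Step 4: timing.** Set side by side, the sections give this order: monitoring starts, needles go in, five minutes pass, endoscopy begins. A reading timed only as before endoscopy fits any point in that order, before or after needle placement.

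Hypotension and low saturation have the same defect in definition. Their size is not estimated here, because the documents give no basis for it.

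**The case against.** The strongest reply is that this is a condensed article. Exact reading times and attribution rules often sit in the CRF, the manuals or the analysis plan, none of which is shown. Monitoring starts before the allocation-specific steps, so a pre-needling reading fits the described sequence. The word periinterventional may be meant to exclude values present beforehand, and nothing says that the first reading is itself classified against Table 2. The endpoints are descriptive, and the prevalence figures are assumed.

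Part of this stands. The timing problem is an ambiguity, not a proven error, and the size is illustrative. But Table 2 is a stated outcome rule, and it reads the same under the narrow interpretation: an unchanged low value during the procedure still qualifies.

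A reader might also infer that the vital signs are compared without using the first reading. The documents do not support that. Further analysis neither names nor excludes adjustment or change scores, and that choice is commonly left to the analysis plan. Nor do they support a claim of systematic bias between arms, since randomization balances pre-existing low values in expectation.

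A further objection concerns the remedy. A count restricted to new onset would mean that a patient starting at a saturation of 91% could never register that complication, however far the value fell. This is right, and the fix below allows for it.

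**Conclusion.** The point holds for the complication definitions and for the timing of the first reading. As written, Table 2 mixes pre-existing low values with procedural events, and no reading is guaranteed to precede treatment. The consequence is inflated absolute rates in both arms and a between-arm comparison diluted towards no difference.

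The size rests on assumptions. A resting heart rate with mean 70-80 and SD 12 puts about 5-20% of patients below 60 beforehand. At 10% already low, all of them counted, and 5% new onset among the rest, about 69% of recorded bradycardia is pre-existing. Fewer such patients, or a rise in rate during the procedure, would reduce that share.

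The effect is confined to secondary and safety results. It is worth correcting because the correction is cheap and a missing pre-needling reading cannot be replaced later.

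**What to change.** 1. State in the protocol and CRF that the first reading is taken before needle placement. Monitoring of saturation and blood pressure is already set up by then. The sentence on monitoring does not name heart rate, so the CRF line should cover all three.
2. Leave the Table 2 cut-offs unchanged. Report heart-rate, blood-pressure and saturation events as new onset relative to the pre-needling reading.
3. Show the all-occurrence counts alongside, together with the change from the pre-needling value in patients who were already below a cut-off, so that worsening is not hidden.
4. As a recommendation only, adjust the two later readings for the pre-needling value by ANCOVA. With an assumed correlation of 0.5-0.7 the variance is 1 − r² = 0.75 to 0.51 of that of a comparison of later values alone. Against change scores the ratio is (1 + r)/2 = 0.75 to 0.85, a smaller gain at the higher correlation. The adjustment is safe only if step 1 is in place.

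The cost is one timing line in the CRF, one sentence of definition and one extra table. Headline complication counts will be lower. The sample size and the primary analysis do not change.

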#### Safety aspects

##### Specification of safety variables

The correct placement of the needles will be checked and if necessary replaced by the physician who performed the acupuncture right before the examination. After endoscopic examination the needles will be checked again. If some of the needles are not in place after examination it will be documented in the CRF.

##### Concomitant medication

Every patient can be switched to systemic sedation at anytime to successfully complete the EGDE if necessary or at the patient's wish. The conversion will be documented in the CRF and the patient's satisfaction will be counted as 5/5 (unacceptable) on the Likert scale. Therefore, the need for systemic sedation is defined as unsuccessful EGDE for both intervention groups.

##### Past medical history

Prior and concomitant illness of the patients will be documented in the CRF.

##### Adverse events and serious adverse events

AEs will be reported to the principal investigator in regular intervals during the course of the study. SAEs will be documented on a special SAE form in the CRF and will be reported to the principal investigator within 24h.

#### Analysis

##### Analysis sets

Each patient's allocation to the different analysis populations (full analysis set (FAS) according to the intention-to-treat (ITT) principle, per protocol (PP) analysis set, safety analysis set) will be defined prior to the analysis. The allocation will be documented in the statistical analysis plan. During the data review, deviations from the protocol will be assessed as "minor" or "major". Major deviations from the protocol will lead to the exclusion of a patient from the PP analysis set.

##### Confirmatory analysis

The null hypothesis H is assessed by testing the intervention effect in a primary analysis using a two-sided chi-square test. In a secondary analysis a binary logistic regression model that takes into account the covariates "intervention" (placebo/acupuncture), age (< 65,≥ 65) and gender will be used. A two-sided type I error rate of α = 0.05 will be applied to the primary and secondary analysis.

Confirmatory analysis will be primarily based on the FAS which is consistent with the intention-to-treat (ITT) principle, by including all patients who were randomized into the two groups. This approach reflects the idea that the study should correspond to the conditions in clinical practice as closely as possible.

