### Number of patients needed

The sample size calculation is based on the two-sided chi-square test for difference with respect to the primary endpoint.

A review of the previous literature identified a randomized controlled trial from Abraham et al. with a group of 419 patients comparing the rate of successful EDGE with and without sedation[12]. In both groups a pharyngeal anaesthesia was performed. This trial showed a successful examination rate of 46% in the group without sedation. A successful examination was defined as a composite score of patient satisfaction with the procedure as well as quality of the examination (technical adequacy) as assessed by the endoscopist. These were determined by the administration of standardized Likert scales (patient satisfaction on a scale of 1-5, quality of examination on a scale of 1-4). An EDGE examination was only counted as successful if the patient rated 1 or 2 on the satisfaction scale and the endoscopist rated 4 on the quality of examination scale. Based on the results from this large trial we decided to adapt the definition of successful EDGE for our trial and use the 46% success rate of the non sedated group as baseline for the sample size calculation. We believe that an increase of the success rate by 15% or more to > = 61% in the acupuncture group would be clinically relevant and therefore could impact clinical practice. To detect this difference at a type I error rate of α = 0.05 (two-sided) with power 1-β = 80%, a sample size of n = 173 evaluable patients per group is necessary (SAS 9.1 proc power). The drop out rate within the intervention is expected to be about 2% overall. Therefore, another 8 patients in total have to be randomized to obtain the required number of evaluable patients. The total number of patients needed to be randomized is therefore 354 (Figure 2).

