##### Minimizing bias

To achieve comparable groups for known and unknown risk factors, randomization will be performed as a block randomization with alternating block size. Allocation to treatment group will be performed by sealed consecutively numbered envelopes prepared by the Institute of Medical Biometry and Informatics of the University of Heidelberg (IMBI). Randomization will be carried out after the patient has signed the informed consent form and will be documented in the case report file of every patient. The allocation will be controlled by a monitor.

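### The decisive chi-square test is valid and meets its 80% power, but it leaves out age and gender, which the plan already models; adjusting for them would be a low-cost gain in efficiency

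*Protocol article*

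**What the plan says.** - **Decisive test.** In the protocol article, Confirmatory analysis, the null hypothesis is assessed "in a primary analysis using a two-sided chi-square test". No covariate enters this test.
- **Adjusted model.** The same section adds, as a secondary analysis, a binary logistic regression with intervention, age (under 65, 65 or over) and gender. The two-sided 0.05 level "will be applied to the primary and secondary analysis".
- **Sample size.** Under Number of patients needed: "The sample size calculation is based on the two-sided chi-square test for difference with respect to the primary endpoint". The inputs are 46% success with placebo and 61% with real acupuncture, giving 173 evaluable patients per group and 354 randomized.
- **Randomization.** Under Minimizing bias: "randomization will be performed as a block randomization with alternating block size". Neither age nor gender is named as a stratification factor.
- **Other analyses.** Under Further analysis, the per-protocol analysis is additional and the secondary variables are descriptive. The adjusted model of the primary endpoint is not placed there.

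**The concern.** The plan has chosen two covariates for its model of the primary endpoint, yet the test that decides the trial uses neither. As no stratification is stated, any chance imbalance in age or gender stays in the primary comparison. If either predicts patient satisfaction or a complete examination, adjustment would remove that noise. The sample size leaves almost no margin above 80% power, so a few points of power from data already collected are worth having.

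There is also a smaller matter of wording. Both analyses of the same hypothesis on the same endpoint stand under the confirmatory heading, and each is given the 0.05 level. No sentence says that the logistic result is supportive only.

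**Working it through.** **1. The plan's own figures.** Inputs from Number of patients needed: p0 = 0.46, p1 = 0.61, difference 0.15, two-sided alpha 0.05 (z = 1.960), power 80% (z = 0.842). The mean rate is 0.535.

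n per group = [1.960 × √(2 × 0.535 × 0.465) + 0.842 × √(0.46 × 0.54 + 0.61 × 0.39)]² / 0.15²

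= [1.960 × 0.7054 + 0.842 × 0.6974]² / 0.0225 = 172.4, rounded up to **173**.

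Power at 173 per group is 80.1% by this formula (79.3% exact). Dropout: 346 / 0.98 = 353.1, rounded up to **354**. Both stated figures reproduce.

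**2. What adjustment would change.** The article gives no age or gender distribution and no prognostic strength, so these are assumptions: 40% aged 65 or over, 50% of each gender, and a range of odds ratios for success. Trials with 173 per arm were simulated with marginal success rates held at 46% and 61% (20,000 replicates) or at 46% in both arms (40,000 replicates). Each data set was analysed with the uncorrected chi-square test and with the planned logistic model (age cut at 65, gender, Wald test).

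| Assumed OR, age / gender | Power, chi-square | Power, adjusted | Gain (points) | Type I error if either test counts |
|---|---|---|---|---|
| 1 / 1 | 79.5% | 80.3% | 0.8 | 5.4% |
| 1.5 / 1.5 | 79.1% | 80.8% | 1.7 | 5.6% |
| 2 / 2 | 79.3% | 82.3% | 3.0 | 5.9% |
| 3 / 2 | 79.3% | 83.5% | 4.2 | 6.2% |
| 4 / 3 | 79.4% | 86.3% | 6.9 | 6.5% |

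Monte Carlo standard errors are about √(0.8 × 0.2 / 20,000) = 0.28 points for power and √(0.05 × 0.95 / 40,000) = 0.11 points for type I error.

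The 0.8 points in the first row are not efficiency. They reflect a slightly liberal Wald test: 5.2% under the null, against 4.8% for the chi-square test. Taking 0.8 off the other rows leaves roughly 0.9, 2.2, 3.4 and 6.1 points.

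**3. Type I error of a single named test.** Used alone, the chi-square test ran at 4.7% to 4.8% and the logistic test at 4.9% to 5.2%. The standardised risk difference ran at 4.7% to 5.6% in one set of simulations and about 5.3% to 5.7% in another. Part of that excess is Monte Carlo error.

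**4. Effect measure.** The marginal odds ratio for 61% against 46% is (0.61 / 0.39) / (0.46 / 0.54) = 1.84. The conditional odds ratio in the adjusted model is 1.86 to 2.04 in the scenarios with prognostic covariates. An adjusted odds ratio is therefore not on the scale of the design target, whereas a standardised risk difference can be read directly against 15 points.

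**The case against.** The strongest reply is that nothing is broken. With no stratification stated, no design factor has to be carried into the analysis. Chance imbalance is already covered by the chi-square test's type I error. The test matches the one used for the sample size and delivers the promised power, and an adjusted analysis is planned anyway. All of this stands. It makes the point one of efficiency, but does not remove the gain.

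A reader might infer that the plan gives away substantial power. The documents do not support that, because they give no prognostic strength. Simulations of the standardised risk difference under other assumptions reached 87.2%, but with an odds ratio of up to 1.75 per decade of age. That is 1.75⁴ = 9.4 between ages 35 and 75, and should not be taken as the expected case.

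A reader might also infer two open chances of a positive result. The text calls the chi-square analysis primary and the logistic one secondary, and the trial is sized on the former. Read that way, a chi-square p of 0.06 is a failed primary analysis whatever the logistic model shows, and type I error stays at about 5%. Even if either result could be claimed, the rate is well below the 1 − 0.95² = 9.75% of two independent tests, because the two are highly correlated. The analysis plan, which is not shown, may settle the model's standing. What remains is a sentence that gives both analyses the confirmatory level.

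**Conclusion.** The primary test is valid and correctly sized; the plan is not in error here. Adjusting the decisive test for age and gender is a worthwhile improvement of uncertain size: about 1 to 3 points of power at odds ratios of 1.5 to 2, about 4 to 7 if the effects are strong, and essentially nothing gained or lost if neither is prognostic. These figures rest on the assumed covariate distribution and odds ratios, and include up to about 0.8 points from the slightly liberal Wald test.

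The error-rate issue is a minor matter of wording. The labels already point to the chi-square test as decisive, and the rise to about 5.4% to 6.5% is conditional on disregarding them.

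**What to change.** In Confirmatory analysis, name one decisive analysis: the intervention effect in the full analysis set, adjusted for age and gender, reported as a standardised (marginal) risk difference with a 95% confidence interval. Keep the unadjusted chi-square test as supportive, and state that it carries no confirmatory claim. Replace the sentence that applies 0.05 to both analyses with one that applies it to the decisive analysis only.

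If the sponsor prefers to keep the chi-square test as decisive, one sentence calling the logistic model supportive, without its own confirmatory level, settles the wording. The efficiency gain is then forgone.

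**Cost.** A few sentences and slightly more programming. No new data or patients are needed, since both covariates are already planned for the model. The standardised estimator may be slightly liberal at this sample size; a small-sample variance correction can address that and should be specified with it. The article states that randomization began in February 2010, so a change of decisive analysis should be documented as an amendment before anyone sees outcomes by group.

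### The secondary logistic model cuts age at 65 without a stated reason; entering age in years would adjust better at almost no cost, and the primary test is unaffected

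*Protocol article*

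**What the plan says.** Under Confirmatory analysis, the Protocol article assesses the null hypothesis by "testing the intervention effect in a primary analysis using a two-sided chi-square test". It continues: "In a secondary analysis a binary logistic regression model that takes into account the covariates" intervention, age and gender. Age is coded in two classes: "age (< 65,≥ 65) and gender will be used". Both analyses are given a two-sided level of 0.05. The section gives no reason for the cut at 65 and names no effect measure for the logistic model.

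Under Number of patients needed, the target is a difference in success rates: "an increase of the success rate by 15% or more to > = 61% in the acupuncture group", from a baseline of 46%. Under Eligibility, patients must be at least 18 years old. The article gives no mean age, no spread and no share of patients aged 65 or over.

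**The concern.** The two-class coding is fixed in the article itself, so it can be reviewed as a stated choice. Each patient's age has to be known to check the age limit and assign the class, so the cut throws away information already in hand. It treats ages 20 and 64 as equal and ages 64 and 65 as different. An age imbalance between the arms that lies within a class is left in the adjusted comparison. This is the only covariate adjustment the article describes.

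A second, smaller matter is scale. The coefficient of a logistic model is a conditional log odds ratio, whereas the trial was sized on a difference of 15 percentage points. If only the coefficient were reported, the adjusted result could not be set directly beside that target.

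**Working it through.** **Inputs.** From Number of patients needed: 46% versus 61%, two-sided alpha 0.05, power 80%, 173 evaluable per group, 2% drop-out, 354 in total. From Confirmatory analysis: age cut at 65. The age distribution and the strength of the age effect are not in the document. They are assumed below and varied.

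**Step 1: reproduce the plan's figure.** With p̄ = 0.535:

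n = [1.960·√(2·0.535·0.465) + 0.8416·√(0.46·0.54 + 0.61·0.39)]² / 0.15² = (1.3825 + 0.5869)² / 0.0225 = 172.4, rounded up to 173 per group.

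346 / 0.98 = 353.06, rounded up to 354. Both figures reproduce, and power at 173 per group is 80.1%. No covariate enters this calculation, so the coding of age cannot change it.

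**Step 2: age information kept by the split.** This is the squared correlation between age and the indicator of age ≥ 65.

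- Normal age: φ(c)² / [p(1−p)], with c = (65 − mean)/SD and p = 1 − Φ(c). For mean 60, SD 15: c = 0.333, p = 0.369, and 0.1424 / 0.2329 = 0.611 is kept, so 39% is lost.
- Uniform age: 3p(1−p). For ages 20 to 90: p = 25/70 = 0.357, and 3·0.357·0.643 = 0.689 is kept, so 31% is lost.

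| Assumed age distribution | Share ≥ 65 | Information lost |
|---|---|---|
| Normal, mean 65, SD 15 | 50% | 36% |
| Normal, mean 60, SD 15 | 37% | 39% |
| Normal, mean 55, SD 15 | 25% | 46% |
| Normal, mean 50, SD 15 | 16% | 56% |
| Normal, mean 45, SD 15 | 9% | 68% |
| Uniform 18–85 | 30% | 37% |
| Uniform 20–90 | 36% | 31% |
| Uniform 40–90 | 50% | 25% |
| Two peaks, at 45 and 75 | 48% | 19% |

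**Step 3: cost to the treatment test.** Losing age information is not the same as losing treatment information, so the two codings were compared directly. The simulation used 346 patients, 1,500 trials per row, and marginal success rates of 46% and 61%. Assumed were age with mean 57 and SD 15, a linear age effect on the log-odds scale, and a gender effect of 0.2 log-odds.

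| Age effect (log-odds per SD) | Chi-square | Logistic, split age | Logistic, age in years | Years minus split |
|---|---|---|---|---|
| 0 | 79.5% | 80.0% | 80.1% | +0.1 |
| 0.3 | 79.7% | 81.6% | 81.4% | −0.2 |
| 0.6 | 79.2% | 81.7% | 83.9% | +2.2 |
| 1.0 | 77.4% | 83.8% | 86.7% | +2.9 |

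The Monte Carlo standard error of each power is about √(0.8·0.2/1500) = 1.0 point. Both models were fitted to the same simulated trials, so their difference is steadier than that, but the first two rows show no difference.

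**Step 4: scale.** 46% versus 61% is a marginal odds ratio of (0.61/0.39)/(0.46/0.54) = 1.84. For the same 15-point difference, the conditional odds ratio is 1.86, 1.93 and 2.09 at age effects of 0.3, 0.6 and 1.0. The risk difference standardised from either logistic model averaged 0.148 to 0.151 throughout, so it recovers the quantity the trial was sized on.

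**The case against.** The strongest reply is that this is a modelling preference in a secondary analysis. The deciding test is the unadjusted chi-square, which compares proportions, matches the sample size calculation and is valid under randomisation whatever the age balance. The two-class model still adjusts for gender and part of age. A cost of 2 to 3 power points needs a strong age effect, for which the article offers no evidence. All of this stands, and it limits the point to a minor one. It does not justify the cut: no reason is given, and age in years costs essentially nothing even when age has no effect.

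A reader might infer more than the document supports:

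- **That at least a third of the age information is lost.** This bound needs normally distributed age with a linear effect. Other shapes in the table lose 19%, 25% or 31%.
- **That the adjusted result will be an odds ratio only.** The article names a model and no reported measure. A risk difference can come from the same model, and the statistical analysis plan, which is not at hand, may provide for it.
- **That age is not collected**, because the Table 1 footnote on personal data lists only "height (cm), weight (kg), gender, smoking customs, chemotherapy, existence of false teeth". Age is an eligibility criterion and a named covariate, so its absence from a footnote in a condensed article does not show this.
- **That the model is the only safeguard against chance imbalance.** The randomised chi-square test already allows for such imbalance in its error rate.

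**Conclusion.** The point holds as a minor improvement to a stated method: age is split at 65 without a reason, and age differences within each class go unadjusted.

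The split loses roughly a fifth to a half of the linear age information under most distributions tried. It loses somewhat more if the mean age is 50 and two thirds if it is 45. The resulting cost to the adjusted treatment test is about 0 to 3 power points: none with a weak age effect, and 2 to 3 with a strong one. These sizes rest on assumed age distributions and a linear age effect. If success really changed in a step at 65, the split would be the right form, but the article does not argue this.

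The primary test, the 173 per group and the total of 354 are untouched, and nothing here invalidates the confirmatory analysis.

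**What to change.** In the secondary logistic model, replace the two age classes with age in years, either linear or as a spline whose knots are fixed in advance. As an optional addition, report the standardised risk difference with its 95% CI from the same model, beside any odds ratio, so that the adjusted result can be read against the 15 points. Keep the two-sided chi-square test as the deciding analysis.

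The cost is one line of analysis wording, settled before unblinding. No new data and no change in sample size are needed.
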